- List the medication(s)/treatment(s) permitted (including rescue medication) and not permitted before or during the trial.

No medications will be administered as part of this trial because the intervention is a skills training. Participant's existing medication (e.g., pain analgesics) will be documented at pre and at post-assessment. Participants will be asked to, where possible, refrain from making changes to their medication throughout the trial and will be asked to advise the research team if they do make changes to their medication during the trial.

- Describe the follow-up period(s) for subjects for each type of intervention.

Follow-up periods for participants in both the treatment and the treatment-as-usual conditions will be as follows:

*Baseline assessment:* Participants in both conditions will complete online self-report assessments via the online Qualtrics survey platform to measure emotion dysregulation, social cognition, pain intensity, depression, anxiety, stress, sleep quality, harm avoidance, emotional effectiveness, coping behaviours, healthcare treatment, and quality of life.

*Post-assessment:* At 9-weeks post baseline assessment, the self-report measures administered during the baseline assessment will once again be completed by participants in both conditions. In addition, participants in the treatment condition will self-report their satisfaction with, and the useability of, the iDBT-Pain intervention and will complete a semi structured interview with a member of the research team. Self-report measures will be completed online via Qualtrics and the semi-structured interview will be via phone or Zoom at a time convenient for the participant.

*Follow-up assessment – 3 months:* At 3 months following the post-assessment the self-report measures administered during the baseline assessment will once again be completed by participants in both conditions.

- Specify any differences between the trial intervention, treatment, placebo arms for the trial.

*Treatment Condition:* Participants in the treatment condition will receive the iDBT-Pain intervention. The iDBT-Pain intervention involves one 60-90 minute introductory session, six 60-90 minute iDBT-Pain sessions delivered by a DBT skills trainer via Zoom in groups of 8 to 12 participants, and one concluding session delivered weekly (every 7 days) over eight weeks. As part of the iDBT-Pain intervention, for the duration of the eight weeks, and for one week after the concluding Zoom session, participants will have continued access to a web app (iDBT-Pain web app) which participants will access on their own smart device (e.g., iPhone or computer) with their own secure password and username. The iDBT-Pain app includes videos and tasks to encourage skills practice between the Zoom sessions and to maintain the skills in the week

following the concluding session. Participants will be provided with a set of clear instructions to set up the app and to access the sessions (Attachment 9).

*Fidelity and Consistency Across Treatment Groups:* Participants in the treatment condition will be in one of two skills training groups consisting of 12 participants for their iDBT-Pain sessions. The structured protocol (see section 10.1) for the iDBT-Pain sessions will ensure treatment fidelity and consistency across the two groups to mitigate effects of confounding factors that may arise due to different groupings.

*Treatment-as-usual condition:* In contrast to the treatment condition, the treatment-as-usual condition will receive no intervention as part of the trial. Participants in the treatment-as-usual condition may receive treatment options as offered by the healthcare professionals they would normally consult with in the community (see Section 10).

Upon conclusion of the study (e.g, following 3-month assessment) all participants will retain (if in the treatment group) or receive (if in the treatment-as-usual group) access to the iDBT-Pain app for personal use on their own smart device.

## 9. Safety and Monitoring

### 11.1 Assessment of Safety Event Report Forms

Safety reports will be assessed on the seriousness, causality, and expectedness of the event to the trial treatment(s), intervention(s), investigational medical product(s), investigational medical device(s). The following are known and expected adverse effects, harms, risks or discomforts associated with trial procedures, treatments or interventions.

#### a) Known Adverse Effects

Provide a detailed list of all adverse effects of the trial intervention that participants may (or have the potential) experience.

DBT skills training is an evidenced-based protocol for emotion dysregulation (Linehan, 2015; Neacsiu et al., 2014). In our pilot trial there were no adverse events (Norman-Nott et al., 2021), and prior research further shows that DBT skills training is a standardised approach with no known side effects reported (Linton, 2010; Sysko et al., 2016). Thus, we do not anticipate any study related adverse events in this current trial.

#### b) Known Harms, Risks or Discomforts

Provide a detailed list of all adverse effects of the trial treatments that participants may (or have the potential) experience.

*Psychological Risks (mild and minimal likelihood):* The aim of the iDBT-Pain skills training is to enable participants to better appraise and express emotions which are impacted by the effect of chronic pain on their lives. On exposure to this information, a very small minority of participants may experience temporary and transient increases in distress. However, this was not observed in our previous study (Norman-Nott et al., 2021). We will also minimise this risk by excluding people with diagnosed psychiatric conditions or mental health disorders (see Exclusion Criteria). If for any reason participants do experience increased distress, they will be able to discontinue the program, and after a discussion with the skills trainer (who will consult with the principal investigator), be referred to alternative sources of support. Participants will never be required to

practice or learn skills more than they would like to, and the skills trainer will not coerce or persuade the individual to keep going with program if the participant wishes to discontinue.

There are no anticipated risks associated with conducting the skills training online or with using Zoom as a tool for this purpose. It is anticipated that by having the skills training online it is an advantage for this population who may struggle with mobility due to chronic pain symptoms making access to a face-to-face session harder than online. To ensure that participants feel comfortable using Zoom and do not experience distress using this platform, they will be taken through a short training on this tool (10 mins) during the introductory session (see Section 10.1). For technical issues with connecting to Zoom, the participants will be advised that they can contact the researchers (e.g., by emailing [[contact]](mailto:[contact])).

*Physical Risks (mild and minimal likelihood):* There may be some discomfort in terms of fatigue by attending up to nine hours of Zoom sessions. To mitigate this, sessions will be spaced evenly throughout the intervention period with one per week over eight weeks (see Section 10.1), with sufficient time between sessions and breaks as necessary. Participants may similarly experience some fatigue and boredom when completing the survey and questionnaires. To mitigate this where possible the short forms of the questionnaires have been selected (e.g., DERs-18).

*MRI risks (mild to minimal likelihood):* MRI is a non-invasive and painless procedure. The MRI equipment has been in routine clinical use for over two decades and is approved by the Australian Therapeutic Goods Administration, the European Union, and the USA Food and Drug Administration. During the MRI scanning, participants may become anxious or claustrophobic. If for any reason a participant becomes uneasy or uncomfortable, they may stop the procedure at any time; a buzzer will be given to hold for this purpose. The scanner makes loud banging noises during the procedure, so earplugs and headphones will be provided to minimise the noise.

There are no risks associated with the MRI process, and there are no short- or long-term side effects. There is a low possibility of nerve stimulation which may manifest as a tingling sensation or twitching; however, this will not be a risk to the participants' health.

Participants will not be allowed to have an MRI examination, if they have any of the following conditions: a cardiac pacemaker; metal fragments in eyes, skin, body; heart valve replacement; brain clips; venous umbrella; history of being a sheet metal worker or welder; aneurysm surgery, intracranial bypass, renal, aortic clips; prosthetic devices such as middle ear, eye, joint or penile implants, joint replacements; hearing aid; neurostimulator; insulin pump; intrauterine device (IUD); shunts/stents; metal mesh/coil implants; metal plate/pin/screw/wire, or any other metal implants; permanent eyeliner, eyebrows. The participants will be asked to fill in an MRI safety form before entering the scanning room. A trained MRI radiographer will be present throughout the whole procedure, monitoring the participant's scanning.

Cerebral MRI is most commonly used in diagnosing neurological diseases, and rarely may find unexpected pathology. In that event, a neurologist from NeuRA's imaging facility, who will look at all structural images, will release the report to the researcher in charge of this study (A/[name]) who would then be responsible for any follow up. If abnormalities should be found, A/[name] would be responsible for advising the participant of the abnormal report and liaising with the participant for the submission of the report to their primary health care provider.

Participants may feel uncomfortable, and/or experience claustrophobia being in the MRI, but we will try to minimise that discomfort by informing them of

the testing environment ahead of time; informing them they can pause or discontinue at any time, and providing noise reducing earplugs.

### **Adverse event and serious adverse event reporting**

DBT skills training is an evidenced-based protocol for emotion dysregulation (Linehan, 2015; Neacsiu et al., 2014), and research shows that DBT skills training is a standardised approach with no known side effects reported (Linton, 2010; Sysko et al., 2016). Thus, we do not anticipate any study related adverse events in this current trial.

Nevertheless, if any adverse events do occur, the IDBT-Pain research team will collect data, document the information and report to the relevant bodies within the timeline as required by the UNSW HREC (detailed below).

Participants will have the ability to communicate with the research staff throughout the study, via email ([contact]) and phone (trial phone number to be confirmed) and can contact them if they have concerns that may be related to, or resulting from any aspect of the trial. If necessary, the participant will also be advised to seek care from their usual health care professional. We will further provide (if necessary) a list of counselling services participants may access (e.g. Beyond Blue, Lifeline etc) (Attachment 10).

Adverse event data will be collected via participant text, phone, or email contact with the IDBT-Pain research team, and the research team will monitor any difficulties participants may be having during the skills training.

For all adverse events an evaluation form will be completed that will include a description of the event, a classification of seriousness, assessment of potential relationship to the intervention, assessment of need for change in the consent or the study activities, a summary of known prior health issues, and event outcome.

## **11.2 Adverse Events or Adverse Reactions**

Adverse events (AE) are considered any untoward medical occurrence in a patient or clinical trial participant administered the intervention, which does not necessarily have a causal relationship with this treatment.

Adverse Reactions (AR) are considered untoward and unintended responses to the trial intervention related to any intervention procedures.

AEs and ARs are assessed using the safety monitoring flow chart. Those classified as "not serious" are assessed by the qualified physician/medical expert specified in section 2 of the protocol. The Qualified Physician cannot delegate this responsibility to other research personnel.

Adverse event reports must be reported to the Principal Investigator within 24 hours of being notified by the participant. All adverse event reports must be recorded in the [UNSW Safety Monitoring Register Template](#).

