Treatment-as-usual: Participants in the treatment-as-usual condition may receive treatment options that can be any of those offered by the healthcare professionals they would normally choose to consult with in the community. In other words, the participants in the treatment-as-usual condition will be advised they will not receive treatment determined by the study or funded by it. It will be explained to the participants that the role of being in this group is very important to the study because the outcomes gained by this group set the bar to know whether the intervention (iDBT-Pain) is any better or not. It will further be explained to these participants that they will have access, at the study conclusion (e.g., following the 3-month follow-up assessment), to the iDBT-Pain web app accessible via their own smart device.

*Data Collection Procedure:* Assessment times for both the treatment and treatment-as-usual conditions will be at baseline, post-intervention (9-weeks post baseline assessment) and at 3 months following the post-intervention assessment. Baseline assessment will begin once 24 participants are in a group and randomised. Assessments will encompass self-report questionnaires (see section 10.1), and eligible participants will be invited to undertake MRI scanning. Questionnaires will be completed online via Qualtrics survey platform and will take a maximum of 90 minutes to complete. MRI scanning will be in-person at NeuRA, Sydney (see section 10.1). Participants will be advised that if they cannot or choose not to participate in the MRI they may still participate in all other aspects of the study. Additionally, post-intervention, qualitative data will be collected from participants in the treatment condition via a semi structured interview with a member of the research team via Zoom or phone call.

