## 10.1 Trial Intervention

- Describe the trial interventions, specify the qualifications and experience required by personnel delegated these responsibilities.

*Trial Intervention:* iDBT-Pain is an online skills training encompassing a total of eight 60-90-minute-long sessions (including an introductory and concluding session), delivered over the internet using Zoom. These sessions will be delivered as part of a group of around 8 to 12 participants and will occur on a Friday lunchtime sometime between 12pm and 2pm AEST approximately every 7 days across eight weeks. For the duration of the eight weeks, and for one week after the concluding Zoom session, participants will have continued access to a web app (iDBT-Pain web app) which participants will access on their own smart device (e.g., iPhone or computer) with their own secure password and username. The iDBT-Pain app includes videos and tasks to encourage skills practice between the Zoom sessions. This intervention is designed to teach DBT skills in mindfulness, emotion regulation, and distress tolerance alongside psychoeducation about chronic pain. Each of the eight session builds on the content of the last to give participants a complete set of skills. This format for the skills training mirrors that used in our successful pilot study where no difficulties in adherence were observed. Nevertheless, to facilitate the completion of all skills by all participants, the iDBT-Pain sessions will be recorded via Zoom. Thus, in the instance that a participant is unable to attend one of the iDBT-Pain sessions they will be sent the session as a recording which they can watch at the earliest opportunity to catch up on the content before the next session. The iDBT-Pain skills training in the current study will follow the study protocol developed and trialled by Norman-Nott et al (2021) and will follow the below session outline:

| Session                       | Module                       | Skills                                                                                                         | Function                                                                                                                                                      |

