## **11.3 Serious Adverse Events**

Serious Adverse Events (SAEs) that result in or lead to one or more of the following and the event is **not related** to the trial intervention:

- The death of a trial participant.

- A life-threatening illness or injury involving a trial participant.
- A participant's permanent impairment of body structure or body function.
- In-patient or prolonged hospitalisation (not for a pre-existing condition or an elective surgery) of a trial participant.
- Medical or surgical intervention to prevent life-threatening illness or injury or permanent impairment to a body structure or function of a trial participant.
- Fetal distress, fetal death or congenital abnormality or birth defect.

SAE reports are classified following the safety assessment flowchart and are assessed by Sponsors Independent Medical specified in section 2 of the protocol. The Sponsors Independent Medical cannot delegate this responsibility to other research personnel. SAE reports are reported to the Coordinating Principal Investigator immediately or within 24 hrs of the event occurring. SAR reports must be recorded in the [UNSW Safety Monitoring Register Template](#).

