#### 11.4 Serious Adverse Reactions

A Serious Adverse Reactions (SAR) is an SAE that is **related** to the trial intervention. SAR reports are classified following the safety assessment flowchart and are assessed by Sponsors Independent Medical expert specified in section 2 of the protocol. The sponsors independent medical expert must determine whether the SAR was expected or unexpected. The Sponsors Independent Medical cannot delegate this responsibility to other research personnel.

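### The adverse-event definition and its collection routes cover the treatment arm more fully than treatment-as-usual, and the SAE and SAR definitions contradict each other

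*Protocol*

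**What the plan says.** Section 11.2 defines an adverse event as "any untoward medical occurrence in a patient or clinical trial participant administered the intervention", whether or not the intervention caused it. Section 10.1 (Trial Intervention) states that "the treatment-as-usual condition will receive no intervention as part of the trial".

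The reporting text in section 9 gives two routes by which events reach the team. The first is "Adverse event data will be collected via participant text, phone, or email contact with the IDBT-Pain research team". The second is that "the research team will monitor any difficulties participants may be having during the skills training". The training is "a total of eight 60-90-minute-long sessions", attended by the treatment arm only. Section 8 adds that after the intervention "qualitative data will be collected from participants in the treatment condition via a semi structured interview".

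For serious events, section 11.3 opens with "Serious Adverse Events (SAEs) that result in or lead to one or more of the following and the event is" and goes on to require that the event be unrelated to the intervention. Section 11.4 then says "A Serious Adverse Reactions (SAR) is an SAE that is" related to it.

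**The concern.** The trial judges the intervention against treatment-as-usual, and its results are meant to inform a full-scale trial. If harms are ever tabulated by arm, a difference should reflect the intervention, not who was covered by the definition or who was in contact with staff. As written, the definition names only people who were given the intervention, and the only active observation takes place in sessions that the control arm does not attend. The protocol itself allows that a small minority may become temporarily more distressed. Without comparable control data, that cannot be set against the background rate in people with chronic pain.

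The serious-event wording raises a separate problem. Causality is built into the definition of an SAE, and the next section then contradicts it. The classification decides how an event is reported, so staff need definitions that they can apply.

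**Working it through.** The protocol states no AE rate, safety sample size or safety test, so there is no figure to reproduce. The check sets the provisions side by side.

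**1. Who can have an AE.** Section 11.2 requires that the participant was given the intervention. Section 10.1 says that the control arm is not given one. Taken literally, an event in a treatment-as-usual participant falls outside the definition.

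**2. How an event reaches the team.**

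| Route or contact | Treatment | Treatment-as-usual |
|---|---|---|
| Participant texts, phones or emails | yes | yes |
| Allocation given by phone or email | yes | yes |
| Surveys at baseline, 9 weeks and 3-month follow-up | yes, no AE item listed | yes, no AE item listed |
| Monitoring during skills training | eight sessions | none |
| Interview after the intervention | about 20 minutes | none |

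Session time in the treatment arm is 8 × 60 = 480 minutes (8 hours) to 8 × 90 = 720 minutes (12 hours). The physical-risk paragraph in section 9 puts it at up to nine hours. On either figure the control arm has none.

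**3. Size of the distortion.** Let p be the true event risk, equal in both arms, and let c_T and c_U be the proportions of events captured in treatment and usual care. The reported risk ratio is (p × c_T) / (p × c_U) = c_T / c_U. The documents give neither capture proportion. With c_T assumed at 0.90:

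- c_U = 0.90 gives 0.90/0.90 = 1.0
- c_U = 0.50 gives 0.90/0.50 = 1.8
- c_U = 0.30 gives 0.90/0.30 = 3.0
- c_U = 0 gives no finite ratio

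The answer only restates the assumption, so none of these values is an estimate for this trial.

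**4. Serious events.** Write S for serious and R for related.

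- Section 11.3: SAE = S and not R.
- Section 11.4: SAR = SAE and R = (S and not R) and R, which is empty.
- Section 11.4(b): a SUSAR is an unexpected SAR, so it is empty too.

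On this reading a related serious event (S and R) is not an SAE, and it cannot be a SAR because a SAR must first be an SAE. The definitions also break the link with section 11.2, where an AE is defined regardless of cause: a serious AE is not always an SAE.

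The class matters for reporting. Section 11.4(b) sends SUSARs to the sponsor's delegate and the ethics committee within 7 calendar days if fatal or life-threatening, and otherwise within 15. Section 11.9 sends single SAE and SAR reports only to a register and an annual report.

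**The case against.** The protocol plans no between-arm safety analysis. The trial objectives list no safety endpoint, and the statistics section has no safety comparison. A comparison may sit in an analysis plan that is not shown. This stands, and it limits the point to what would happen if rates were shown by arm. An analysis plan could not, however, recover events that were never defined or asked about.

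A reader might infer that treatment-as-usual has no planned contact. That is not so. Those participants are told their allocation by phone or email, complete all three surveys, and are asked to report medication changes. The surveys include the BDI and healthcare utilisation questionnaire at every timepoint and the PGIC at the two later ones. These could reveal deterioration in either arm, but the protocol does not designate them as AE data.

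A reader might also infer that the control arm's event count must be zero. This rests on one phrase in section 11.2. The seriousness criteria in section 11.3 refer to trial participants generally, the contact channel is open to all throughout the study, and nothing forbids recording a control event.

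On serious events, the evident intent is that unrelated SAEs and related SARs together cover every serious event. Both go to the same independent medical expert, and the AE form records seriousness and relationship separately. Misclassification is therefore possible but not shown. The contradiction in wording remains, and even on the intended reading a count of SAEs leaves out the related ones.

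The safety and AE forms (Attachments 11 and 12), the full questionnaires (Attachment 5) and the flow chart are not shown and may add detail. The absence of a scheduled AE question is established only from the assessment table.

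**Conclusion.** The point holds as one of unequal ascertainment plus contradictory definitions. Section 11.2 read literally leaves out the control arm, the second collection route reaches only the treatment arm (8 to 12 hours of sessions against none), and no scheduled AE question is visible for either arm. Any AE rates by arm would be compared with unequal ascertainment. The size of the resulting bias cannot be derived from the documents.

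The stronger conclusion that harms cannot be compared at all is not supported. Control events can be reported and recorded, so the problem is bias and not impossibility.

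Sections 11.3 and 11.4 contradict each other. Read literally, the SAR and SUSAR classes are empty. Read by intent, all serious events are covered but an SAE count omits related ones. This second part would not by itself prevent a comparison between arms. The conclusion rests on the protocol text alone, and on reading the text, phone and email route as contact that participants initiate.

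**What to change.** - In section 11.2, define an AE as any unfavourable medical event in any randomised participant, in either arm, from randomisation to the 3-month follow-up.
- In sections 11.3 and 11.4, define an SAE by the seriousness criteria regardless of relatedness, and a SAR as the related subset. The SUSAR class then follows as the unexpected SARs.
- Add one AE item, worded identically for both arms, to the 9-week and 3-month Qualtrics surveys. Base any between-arm comparison on that item, and list spontaneous and in-session reports separately.

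The cost is a rewording of three short sections and one item in surveys that both arms already complete. The downside is that more minor events will be reported and need classifying.

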At baseline assessment, the questionnaires will be self-reported by participants sequentially online via Qualtrics and will be completed in the same manner post-intervention (i.e., 9 weeks after baseline and at 3 months follow-up). The full questionnaires can be seen in Attachment 5

**Brain Imaging:** Participants in the skills training group who are eligible and interested will attend the MRI facility at NeuRA for imaging assessment at baseline and post-intervention. The MRI equipment has been in routine clinical use for over two decades and is approved by the Australian Therapeutic Goods Administration. Each MRI session (pre-intervention, and post-intervention) will be an identical 60-minute multimodal scan procedure conducted with a Philips Ingenia 3T MRI scanner. Prior to scanning, per safety policy at NeuRA, all participants will complete an MRI safety form to probe for metal in the body or other contraindications. This form will be reviewed by a radiographer before a participant is allowed to enter the scanner room. Structural, functional and biochemical neuroimaging data will be collected.

**Semi-Structured Interview:** Participants will be asked by a member of the research team questions about the iDBT-Pain skills training to attain qualitative data about areas that are effective and aspects that could be improved (Attachment 8). The interview will be conducted by a member of the research team with each participant individually by telephone or via Zoom. The interview will take approximately 20-minutes and will be conducted at a time convenient to the participant. The participants responses will be entered by the researcher directly into a form in Qualtrics and will be stored in accordance with the steps detailed in Section 10. The semi-structured interview will not be recorded.

- Specify how and when the intervention will be administered to trial participants. Indicate the names of the products to be used and provide the instructions for administration.

The iDBT-Pain skills training encompasses the iDBT-Pain sessions administered online via Zoom and the iDBT-Pain web application accessed via smart device (e.g., smart phone, tablet, computer). Participants in the treatment group will receive the intervention when 24 participants have been recruited and randomised and after baseline assessment. The administration will adhere to that of our previous trial (Norman-Not et al, 2021).

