## **11.6 Urgent Safety Measure (USM)**

A measure that is taken to eliminate an immediate hazard to a participant's health or safety. Significant safety issues where an urgent safety measure is required to be taken to eliminate an immediate hazard must be classified as a significant safety issue requiring an urgent safety measure. The Human Research Ethics Committee and the Sponsor's Delegate must be notified of any significant safety issues that meet the definition of an urgent safety measure should be notified within 72 hours. Examples include:

- a serious adverse event that could be associated with the trial procedures and that requires modification of the conduct of the trial
- a patient population hazard, such as lack of efficacy of an intervention used for the treatment of a life-threatening disease.

USM reports must be recorded in the [UNSW Safety Monitoring Register Template](#).

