## 11.9 Reporting of Clinical Trial Safety Monitoring Reports

Single case reports of Adverse Events Adverse Reactions, Serious Adverse Events (SAEs), Serious Adverse Reactions (SARs), reports do not need to be reported to the UNSW Sponsor's Delegate or the HREC. All single case reports must be recorded in a safety monitoring register and are reported to the UNSW Sponsor's Delegate annually.

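### The event form and the SAE and SAR definitions tie relatedness to the skills training, so an unexpected serious MRI injury can miss the SUSAR route, although the protocol elsewhere recognises harm from trial procedures

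*Protocol*

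**What the plan says.** **What the intervention is.** Under 10.1 Trial Intervention, "iDBT-Pain is an online skills training encompassing a total of eight 60-90-minute-long sessions". The same section describes brain imaging separately: "Participants in the skills training group who are eligible and interested will attend the MRI facility at NeuRA for imaging assessment", at baseline and again after the intervention.

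**Where procedures count.** Section 11.1 introduces its list as the "known and expected adverse effects, harms, risks or discomforts associated with trial procedures, treatments or interventions". That list has an entry beginning "MRI risks (mild to minimal likelihood", followed by contraindications. Section 11.6 gives, as an example calling for an urgent safety measure, "a serious adverse event that could be associated with the trial procedures and that requires modification of the conduct of the trial".

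**Where only the intervention counts.** The paragraph on adverse event and serious adverse event reporting says the evaluation form records the possible relationship to the intervention; it names no other trial procedure. Section 11.3 defines an SAE as a serious event not related to the trial intervention, and 11.4 defines a SAR as one that is related to it. A SUSAR is an unexpected SAR. The adverse reaction definition in 11.2 is less clear-cut: "Adverse Reactions (AR) are considered untoward and unintended responses to the trial intervention related to any intervention procedures".

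**What follows from the class.** SUSARs go to the Sponsor's Delegate and the HREC within 7 calendar days if fatal or life-threatening, and within 15 otherwise. For single AE, AR, SAE and SAR cases, 11.9 says the "reports do not need to be reported to the UNSW Sponsor's Delegate or the HREC". They go into a register sent to the Delegate each year.

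**The concern.** The scan is done for the trial, so a serious injury in it is harm caused by taking part. The rule that sorts serious events, however, asks only whether the skills training was responsible. A foreseen source of trial harm therefore has no relatedness category of its own, and its formal label becomes unrelated. The label matters because it decides whether an unexpected serious event has an automatic, timed, individual report to the Sponsor's Delegate and the HREC, or depends on someone making a further judgement. The baseline scan shows the problem most clearly: the intervention starts only after the baseline assessment, so harm from that scan cannot be a response to it.

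**Working it through.** No figure in the plan is in dispute, so the check is to trace one case through the text: a serious, unexpected injury caused by the scanner.

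1. **Is it related, as the text stands?** Section 10.1 equates the intervention with the skills training, and MRI is an assessment. The form, 11.3 and 11.4 all test against the intervention. Literal answer: not related, hence an SAE.
2. **Who hears of an SAE?** Under 11.3 the Coordinating Principal Investigator within 24 hours, and the sponsor's independent medical expert, who must assess it personally. Under 11.8 and 11.9 it is entered in the register and reaches the Sponsor's Delegate annually, and the HREC if required. No single report to either is required.
3. **What if relatedness covered trial procedures?** The event would be a SAR. If it was also unexpected, it would be a SUSAR, reported singly within 7 or 15 days.
4. **When does the difference matter?** Only for unexpected events. An expected SAR is exempt from single reporting under 11.9 just as an SAE is.
5. **Is a serious scanner injury unexpected?** The known-harms section mentions anxiety, claustrophobia, noise, and tingling or twitching, and lists contraindications. It also says that the MRI process carries no risks. On neither reading is a serious injury listed as expected, so that contradiction does not change the class. It does leave the expectedness reference inconsistent.
6. **Which routes remain open without relatedness?** Section 11.5 (significant safety issue, 15 calendar days) and 11.6 (urgent safety measure, 72 hours). Each depends on a judgement about the issue, not on its link to the skills training.

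| Reading | Class | Single report to Delegate and HREC |
|---|---|---|
| Relatedness to the intervention (current text) | SAE | Only if 11.5 (15 days) or 11.6 (72 hours) is invoked |
| Relatedness to intervention or procedure | SUSAR | 7 or 15 days, automatic |

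**Scans exposed.** No number of MRI participants is planned. The ceiling is 2 scans × treatment-arm size. With 50 per arm (section 6), 2 × 50 = 100, of which 50 come before the intervention. Sections 5 and 8 still state 48 participants; assuming an equal split, 48 / 2 = 24 in the treatment arm and 2 × 24 = 48 scans, 24 of them before the intervention. Uptake and MRI eligibility will lower either figure by an unknown amount.

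**Two drafting points in the same definitions.** Section 11.4 calls a SAR a kind of SAE, while 11.3 confines SAEs to unrelated events. Section 11.2 describes adverse events in participants who have been given the intervention, which arguably leaves out harm at the baseline scan.

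**The case against.** A reader might infer that a serious MRI injury could not reach the sponsor or the HREC individually, and that scanning could continue without their knowledge. The text does not support that. Every SAE goes to the Coordinating Principal Investigator and the sponsor's own medical expert. The event form also asks whether the consent or study activities need to change, which prompts the further routes. Sections 11.5 and 11.6 do not depend on relatedness to the skills training, and 11.6 names trial procedures. Under 11.9 a), the Trial Management Group reviews safety information and must seek the advice of the HREC and the Sponsor's Delegate before carrying out a risk plan. A scanner injury that exposed a fault in MRI screening would plausibly be caught by one of these.

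A reader might also infer that relatedness is judged against the skills training throughout. That is too absolute. Section 11.2 speaks of intervention procedures, a term it does not define, and MRI is described within the section headed Trial Intervention. Events are classified with the flow chart in 11.7 and recorded on attached forms; neither is visible here, and they may treat procedures more broadly.

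These points narrow the concern without removing it. The other routes are conditional: an isolated serious injury judged neither a significant safety issue nor a reason to change the trial has no required single report. The mention of procedures in 11.2 is absent from 11.3, 11.4 and the described form, which decide how a serious event is classed. If the flow chart is broader, it disagrees with the written definitions and the two need aligning anyway.

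**Conclusion.** The concern holds in limited form. The protocol is inconsistent about whether harm from trial procedures counts as related. On the literal wording, an unexpected serious MRI injury is classed as unrelated and loses the automatic SUSAR report, leaving notification of the Sponsor's Delegate and HREC to a discretionary judgement under 11.5 or 11.6. The gap is confined to unexpected serious events for which neither judgement is made. Its frequency cannot be estimated from the protocol; only the ceiling of two scans per treatment-arm participant is known. The conclusion assumes that intervention means what 10.1 says it means, and that the unseen flow chart and forms follow the written definitions. The documents do not support a claim about how related events will be counted in publications, since they do not describe it.

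**What to change.** - In 11.2 to 11.4 and in the description of the event form, define relatedness as relation to the trial intervention or any trial procedure, including MRI, so that these agree with 11.1 and 11.6. Have the form record which of them is suspected.
- Extend the causality sentence in 11.1 in the same way, and word the adverse event definition so that it covers baseline procedures.
- In the same edit, remove the conflict between 11.3 and 11.4 over whether an SAE can be related.
- Check that the flow chart in 11.7 and the attached safety forms use the same definition.
- Reconcile the statement that the MRI process has no risks with the MRI risks and contraindications beside it.

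The cost is a wording amendment and one extra item on the event form. No assessment, visit or analysis is added.
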